For our calculations, we will use the normal distribution assumption and explore this using a normal plot and goodness of fit test. If violations are found, non-parametric tests or transformations will be utilized. Variance equivalence will be tested using the F-test. Our protocol is designed to assure sample independence and adherence will be closely monitored. Before beginning the main statistical analyses, baseline variable levels across groups will first be considered to assess group equivalence. If the groups are not balanced on any baseline characteristics, these factors will be considered as variables in later multi-variate regressions.

The Centers for Disease Control defines Gulf War Illness (GWI) or Complex Multisymtom Illness (CMI) as the presence for at least 6 months of one or more self-reported symptoms from at least two clusters of symptoms: Cluster A (fatigability), Cluster B (Mood and Cognition), Cluster C (Musculoskeletal) (10). A single measure of severity that addresses all possible presentations of GWI does not exist. Thus we chose to use as the main outcome a general measure of health. Our primary outcome, the SF-36 (53) is a 36-item measure of global health. It is well recognized with good reliability and validity. Items address multiple aspects of physical and mental health as well as functionality. Eexperience to date from nearly 400 randomized controlled clinical trials suggests that the SF-36 is also a useful tool for evaluating the benefits of alternative treatments (88).

Comparisons between the treatment and wait-list groups will be based on improvement in SF-36 scores. We are considering the primary outcome to be the Physical Component Summary score of the SF-36. We chose to use the SF-36 in order to show general health related quality of life in this population with very diverse complaints. The Physical component subscale was chosen because it focuses on 2 of the three Centers for Disease Control GWI clusters (fatigue and musculosketal complaints). Statistically we will test mean differences between groups following 2 months of treatment using Student’s t-tests at an alpha=0.05. Analyses of secondary outcomes will include a test for mean differences between groups using student’s t-tests at an alpha=0.05.

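### The primary PCS comparison switches to an unnamed non-parametric test or transformation if non-normality is declared, so it may no longer estimate the 7-point mean difference the trial is sized on

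*Protocol*

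**What the plan says.** Protocol Section 18 (Data Analysis) opens with a rule for the calculations in general: "we will use the normal distribution assumption and explore this using a normal plot and goodness of fit test". The consequence follows, and after it a separate sentence on variances that states no action: "If violations are found, non-parametric tests or transformations will be utilized. Variance equivalence will be tested using the F-test".

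The same section defines the primary outcome ("We are considering the primary outcome to be the Physical Component Summary score of the SF-36") and its test: "Statistically we will test mean differences between groups following 2 months of treatment using Student’s t-tests at an alpha=0.05".

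Section 12 (Sample Size Justification) sizes the trial on a 7-point between-group difference in PCS with an SD of 20, and calls a 7-unit improvement clinically relevant.

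The goodness-of-fit test, its threshold, the non-parametric test, the transformation and the effect measure to report after a switch are not named. No sentence takes the primary outcome out of the rule.

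**The concern.** Taken together, these statements make the t-test of means a default that gives way to something else depending on the trial's own data. Two things are at stake.

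- **The target.** The sizing and the relevance threshold are both in mean PCS points. A rank test addresses whether values in one arm tend to exceed those in the other, and a t-test on a transformed scale addresses a difference on that scale. Neither gives a difference in mean PCS to set against 7 points.
- **The room for choice.** A plot is part of the trigger, so the decision to switch is partly a judgement. After it, any non-parametric test or transformation is admissible.

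This is more than detail left for an SAP. The Protocol commits to a switching rule, and an SAP that fixed a single mean-difference analysis would depart from it.

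**Working it through.** **Inputs.** From Section 12: 60 per group, a difference of 7 points, SD 20. From Section 18: alpha 0.05, Student's t-test, PCS at 2 months. Two-sided testing is assumed, as sidedness is not stated.

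**1. The plan's own figure.** The standard error of the difference is 20 × √(2/60) = 3.65. Power = Φ(7/3.65 − 1.96) = Φ(−0.04) ≈ 48%, against the stated 80%. The stated power does not follow from these inputs. The effect-size formula in Section 12 is a figure that is not shown, so it could not be checked. That is a separate matter. It is given here because the simulated t-test power below (about 49%) should match it, and does.

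**2. Assumptions needed to simulate the rule.** The Protocol names none of these:
- Shapiro-Wilk at 0.05 on residuals pooled across arms.
- If it rejects, Mann-Whitney; otherwise a t-test.
- Welch's version after a significant F-test. With equal arms this hardly matters: Student and Welch rejection rates agreed to within 0.1 percentage point.
- Four outcome shapes, each scaled to SD 20. The real shape of PCS here is unknown.

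There were 3,000 trials per scenario with 60 per arm. The simulation error at a 5% rate is √(0.05 × 0.95/3000) = 0.4 percentage points.

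**3. Equal spread (SD 20 in both arms).**

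| Shape | Switch taken | Type I error, gated rule | Type I error, Welch | t and Mann-Whitney disagree, 7-point shift | Power, t | Power, Mann-Whitney |
|---|---|---|---|---|---|---|
| Normal | 5% | 5.0% | 5.0% | 8% | 49% | 47% |
| t, 5 df | 62–64% | 5.0% | 4.3% | 13% | 49% | 56% |
| Gamma, shape 4 | 98% | 4.7% | 5.1% | 11% | 49% | 54% |
| Gamma, shape 2 | 100% | 5.1% | 5.0% | 18% | 49% | 63% |

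With identical distributions the gated rule is close to nominal. The disagreement column counts all trials, whether or not the switch was taken. With normal data the switch is taken in only 5% of trials, so it can change the conclusion in at most that share. With gamma shape 2 it is always taken, so the 18% applies in full.

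**4. Equal means, unequal spread (SD 20 versus 30).**

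| Shape | Gated rule rejects | Welch rejects |
|---|---|---|
| Normal | 5.0% | 4.6% |
| Gamma, shape 4 | about 8–9% | about 5% |
| Gamma, shape 2 | 14.5% | 5.5% |

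The reason can be shown by hand for shape 2. A gamma(2) variable has mean 2, SD √2 and median 1.678. Centred at a mean of 0 and scaled, its median is (1.678 − 2)/√2 × 20 = −4.6 points in one arm and (1.678 − 2)/√2 × 30 = −6.8 in the other. The means are equal but the medians differ by about 2.3 points, and a rank test responds to such a difference. An exponential shape gives 27.4% under the gated rule, but that is extreme for a summary score and the conclusion does not rest on it.

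**5. Is the switch needed?** Across all these scenarios Welch's test rejected a true null in 4.3 to 5.5% of trials. At this sample size the normality check protects the comparison of means against nothing that was tried.

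**The case against.** The strongest reply is that Section 18 names the primary test specifically, that this test matches the sizing, and that the target moves only if a violation is declared for PCS. That is correct, and the point is stated with that condition. It does not remove the point, because the rule covers the calculations generally and has no exemption for the primary outcome. Naming a particular goodness-of-fit or rank test could be left to an SAP, but allowing the primary target to change is already fixed in the Protocol.

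A reader might infer three stronger things that the document does not support.

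- *That the F-test helps choose the primary test.* No action is attached to it. Its high false-alarm rate with non-normal data (about 20% for gamma shape 2 or t with 5 df) would matter only if it were a gate, and none is described. What can be said is that it serves no stated purpose.
- *That the rule materially inflates type I error in general.* Rates of 6.3 to 8.2% come from taking the smallest of four p-values whatever the normality check shows. The Protocol opens the alternatives only after a declared violation, and a single gated fallback stays near 5% when the arms have identical distributions. Logs and square roots are also undefined for negative improvement scores without an arbitrary shift.
- *That normality will be judged with arms revealed.* The trial is unblinded, but the Protocol does not say how the check is run, and it could be done on pooled data.

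One part of the reply stands in full: with skewed or heavy-tailed data and a pure shift, the rank test has more power.

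**Conclusion.** The point holds in a limited form. Section 18 makes the primary comparison conditional on a normality check of the trial's own data, with an open choice of fallback. If that branch is taken, the result is no longer an estimate of the difference in mean PCS points used for sizing.

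The harm is a data-dependent target rather than a generally inflated error rate. Under the assumed gated rule, type I error is about 4.5 to 5.5% with identical distributions. It is wrong for a mean difference only when skew and unequal spread occur together: about 8 to 15% with gamma shapes 4 and 2 and SD 20 versus 30. Nothing in the Protocol shows that PCS behaves this way, so these figures are a range under assumptions and not a prediction. This should be corrected, and a wording change is enough.

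**What to change.** In Section 18, make the primary analysis the difference between arms in mean PCS at 2 months, adjusted for baseline PCS with heteroscedasticity-robust standard errors, or Welch's t-test if no covariate is used. Report it with a 95% confidence interval in PCS points, and state that it applies regardless of any distributional check. Delete the switching rule for the primary outcome, and delete the F-test. Name one rank test, for example Wilcoxon, as a sensitivity analysis that cannot replace the primary result.

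The cost is a wording change. With equal arms, Welch's test loses essentially nothing against Student's. The real downside is power relative to a rank test if PCS is markedly skewed or heavy-tailed: in the shift scenarios above, 49% against 54% (gamma shape 4), 56% (t with 5 df) or 63% (gamma shape 2). In return, the result stays on the scale of the 7-point threshold.

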**GWI Registry**

**“Opt Out” letter**

**Opted Out (refused)**

**Advertisements**

**Initial Screening**

**(Telephone)**

**INELIGIBLE**

**Medical Screening**

**INELIGIBLE**

**Eligible Volunteers**

**Treatment**

**Waitlist**

**Follow-up**

**Follow-up**

**`**

12. Sample Size Justification.

Our study is designed to give us adequate power to detect clinically meaningful differences between treatment groups. Previous acupuncture research using our main outcome, the SF-36, in pain conditions (41,52) show a consistent standard deviation of 20 points in the Physical Component Summary score of the SF-36 for both baseline values and change scores. Sixty individuals per group (total n=120) would offer us a power of 80% to detect the difference between groups of 7 points. Using Cohen’s d estimation of effect size (20):

[figure not shown]

A sample size of 60 will allow us to see a moderate effect. In further support of our main outcome a 7 unit improvement has been shown to be clinically relevant (97,55,78).

Although we do not expect attrition to be large, we expect a dropout rate of no more than 10% by the 8 week endpoint. This trial is longitudinal which could increase drop-out rate. Still a veteran’s population will be less mobile and may have fewer other options for care; both of these factors should increase adherence. We will thus oversample to a target sample size of 67 volunteers per group to assure that our power to detect effects is maintained. The resulting overall sample will be 134 (one treatment group and one wait list group).

13. Description of Informed Consent Process.

The informed consent process will occur in two stages. Verbal informed consent will be administered prior to the initial telephone screening, and written informed consent will be administered in person, at the start of the screening visit.

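### The primary t-test, ambiguous between change and 2-month score, makes poor use of baseline PCS; a prespecified ANCOVA would be more precise at no cost

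*Protocol*

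**What the plan says.** Section 18 (Data Analysis) of the protocol names the variable: "We are considering the primary outcome to be the Physical Component Summary score of the SF-36". It then describes the comparison in two ways. One sentence reads: "Comparisons between the treatment and wait-list groups will be based on improvement in SF-36 scores". The sentence that defines the test reads: "Statistically we will test mean differences between groups following 2 months of treatment using Student’s t-tests at an alpha=0.05". Neither names a covariate, and improvement is not defined by a formula. Secondary outcomes get the same kind of t-test.

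The same section sets out a baseline check: "Before beginning the main statistical analyses, baseline variable levels across groups will first be considered to assess group equivalence". Its consequence is: "If the groups are not balanced on any baseline characteristics, these factors will be considered as variables in later multi-variate regressions". No criterion for imbalance, no list of candidate factors and no regression model is given.

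Section B (data collection instruments) lists the SF-36 at baseline, endpoint and follow-up, so baseline PCS will be available. Section 12 (Sample Size Justification) says that earlier acupuncture studies "show a consistent standard deviation of 20 points in the Physical Component Summary score of the SF-36 for both baseline values and change scores".

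**The concern.** There are two separate weaknesses.

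The first is the primary test. The two sentences describe different estimators. A t-test on the 2-month score gives baseline PCS a weight of zero. A t-test on change gives it a weight of one. ANCOVA estimates the weight from the data. With equal SDs at the two times the best weight is the correlation between them, so both t-tests lose precision whenever that correlation lies strictly between 0 and 1. What is at stake is power, in a trial whose planned size gives little room to lose any.

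The second is how covariates are chosen for the later regressions. After randomisation, a baseline difference between arms is chance. A covariate earns its place by predicting the outcome. Under the stated rule, a strong predictor that happens to be balanced stays out, and a weak one that happens to differ goes in.

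**Working it through.** **Inputs.** From section 12: difference 7 points, SD 20 for baseline and for change, 60 per arm, stated power 80%. From section 18: alpha 0.05, with sidedness not stated and taken here as two-sided. The baseline to 2-month correlation r is not given.

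**The plan's own figure.** The standard error of a difference in means is 20 × √(2/60) = 3.65, so the noncentrality is 7/3.65 = 1.92. Power by the noncentral t is 47.7%, not 80%. One-sided it would be about 60%. This shortfall is a separate matter and serves here only as the reference point.

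**Implied correlation.** Var(change) = SD_base² + SD_2m² − 2r × SD_base × SD_2m. With all three SDs equal to 20, 400 = 800 − 800r, so r = 0.5. The assumption is that the 2-month SD is also 20.

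**ANCOVA at r = 0.5.** Residual SD = 20 × √(1 − 0.25) = 17.3, which is 25% less variance. That is worth 60/0.75 = 80 per arm in a t-test. The standard error is 17.3 × √(2/60) = 3.16, the noncentrality is 7/3.16 = 2.21, and power is 59.3%. The difference detectable with 80% power falls from 10.2 to 8.9 points. Reaching 80% power for 7 points takes about 97 per arm, against about 129 for the t-test.

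**Other correlations.** Score SD 20 at both times, 60 per arm, 7 points, two-sided 0.05. The change-score SD is 20 × √(2(1 − r)).

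| r | t-test, 2-month score | t-test, change | ANCOVA |
|---|---|---|---|
| 0.3 | 48% | 36% | 51% |
| 0.5 | 48% | 48% | 59% |
| 0.6 | 48% | 57% | 66% |
| 0.7 | 48% | 69% | 76% |
| 0.8 | 48% | 85% | 89% |

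Only the r = 0.5 row agrees with a change SD of 20 when the score SD is 20 at both times. The other rows show sensitivity.

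**Other 2-month SDs.** Keep the baseline and change SDs at 20 and vary the 2-month SD, so that r = SD_2m/40.

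| 2-month SD | r | t-test, 2-month score | t-test, change | ANCOVA |
|---|---|---|---|---|
| 18 | 0.45 | 56% | 48% | 66% |
| 20 | 0.50 | 48% | 48% | 59% |
| 22 | 0.55 | 41% | 48% | 54% |
| 24 | 0.60 | 35% | 48% | 51% |

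ANCOVA has the highest power in every row of both tables. The assumptions change the size of the gain, not its direction.

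**The imbalance rule.** As a stress test, suppose that the rule did select the primary test: ANCOVA if baseline PCS differs at p < 0.05, otherwise a t-test on the 2-month score. In a simulation of 40,000 trials with 60 per arm and r = 0.5, type I error was 4.4% and power 48%, against 59% when ANCOVA was always used. Even on that reading, the cost is power and not false positives.

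**The case against.** The case for leaving the plan alone has four parts.

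*Baseline is already used.* A reader might infer from the test sentence that baseline PCS is discarded. The sentence on improvement most naturally means a change score, and section 12 quotes an SD for change scores, so the documents do not support that inference. This stands. What remains is that the two sentences need reconciling and that a change score is less efficient than ANCOVA.

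*The primary test is fixed.* A reader might infer that the baseline check lets chance pick the primary model. It does not: unbalanced factors go into later regressions, and nothing says that these replace the t-test. This also stands, so the criticism of the trigger is confined to those regressions. Nor can one put a probability on some factor being flagged, because the protocol gives neither a threshold nor a count of factors, and its mood, anxiety, depression and fatigue scales overlap.

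*The t-test is valid.* Under randomisation both versions are unbiased, and regression to the mean acts on both arms alike. This stands. The point concerns precision and prespecification, not bias or type I error.

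*Covariates belong in a statistical analysis plan.* This is true of a covariate list. But the protocol itself names an unadjusted test and writes down the imbalance trigger, so an analysis plan that used ANCOVA as primary would depart from it.

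It is also fair that the gain over a change score narrows at high correlation: 7 percentage points at r = 0.7 and about 3 at r = 0.8.

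**Conclusion.** The point holds as one of efficiency and clear prespecification. The primary t-test is valid but ambiguously defined, and it uses baseline PCS inefficiently or not at all, depending on which sentence governs. At the protocol's own SDs, with a 2-month SD of 20 assumed, ANCOVA raises power for 7 points at 60 per arm from about 48% to about 59%. Against a change-score test the gain is larger at low correlation (51% against 36% at r = 0.3) and smaller at high correlation (76% against 69% at r = 0.7).

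A reader might hope that ANCOVA rescues the sample size. At r = 0.5 it does not: 59% is still well below the stated 80%, and that claim has to be corrected in its own right.

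The imbalance trigger is a poor selection rule for the later regressions, but it does not undermine the primary result. Overall this is a change that should be made, not one that threatens the trial's validity.

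**What to change.** In section 18, replace the two sentences on the primary comparison with one model: ANCOVA of 2-month PCS on randomised arm with baseline PCS as covariate, two-sided alpha 0.05, reporting the adjusted mean difference and its 95% confidence interval. Analyse each secondary scale in the same way with its own baseline value. Replace the imbalance trigger with a short list of prognostic covariates, named before the data are seen, for any supportive regressions, and state that these are supportive. Present baseline characteristics descriptively.

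The cost is an amendment to the protocol text and matching wording in the analysis plan. SF-36 is already scheduled at both visits, so no further data, visits or participants are needed.

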We will be collecting a small blood sample at the three data collection points and a research assistants will immediately transport the blood on ice to [name] lab. We are collecting and analyzing these data to better understand the mechanisms of GWI and changes associated with acupuncture. We are focusing on inflammatory changes, immune function, and markers of stress. For example we are interested in the relationship between acupuncture treatment, reported stress, and immune function. Multiple studies have looked at this relationship. For example recent research suggests that acupuncture modulates serum concentrations of inflammatory cytokines; for example, acupuncture reduces cytokine levels in a rat model of inflammation (79) and in asthmatic patients receiving a gentle form of Korean acupuncture (42). It is not surprising then that we have found in our IBS data set that individuals with greater decreases in reported stress had associated immunological changes as measured by a reduction in the percentage of circulating activated T-lymphocytes (CD69+). Toward the exploration of immunophenotyping, blood will continue to be collected with patient consent at the initial screen, at midpoint and at follow up. Mononuclear cells will be stained with a panel of antibodies (DAKO Cytomation) against markers of leukocyte differentiation and activation and analyzed using the Cell Quest program as described above. In parallel, serum cytokine levels (IFNγ, IL-2, IL-2R, IL-7, IL-4) will be measured by ELISA (R&D systems) and serum cortisol levels, as a surrogate biological marker for stress, by a radioimmunoassay. The evaluations at 3 different time points will enable us to identify immunological markers that are predictive of clinical response to acupuncture treatment (initial point) or are associated with it (endpoint). Initial analysis will be performed using ANOVA factorial with Bonferroni correction for multiple comparisons and ANOVA repeated measures for the overtime changes in immune status. If the results of this analysis warrant, a feature selection multivariate analysis will be performed that takes into account higher order interactions among the variables.

18. Data Analysis.

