As GWI is a complex disease with multiple symptom manifestations, we have included measures of global change as well as changes in specific symptoms of interest. These include areas suggested in the Program Announcement as well as one tailored measure described in Appendix 8) that allows volunteers to identify and report changes in their most important symptoms. Our secondary analyses will include a within-groups comparison within CDC clusters for changes baseline to endpoint (2 months of treatment). Cluster A, fatigability, will be assessed using by the Multidimensional Assessment of Fatigue (85). Cluster B, mood and cognition, will be assessed using The Profile of Mood States (62). Cluster C, musculoskeletal complaints, will be assessed using the McGill Pain Scale (55). All of these scales are well recognized in the scientific literature and have shown good reliability and validity.

Our measurements include:

Screening:

- Primary Care Evaluation of Mental Disorder (Prime MD) (81)

Data Collection:

- - The Sf-36 (53)
- Multidimensional Assessment of Fatigue (85)
- The Profile of Mood States (62)
- Pittsburg Sleep Quality Index (34)
- Measure Your Medical Outcomes Profile (40)
- Beck Anxiety Inventory (63)
- McGill Pain Scale (55)
- Carroll Depression Scale (14)
- Social support, Social Networks, and Stress (56-7)
- Medication use and Expectations for Treatment
- Blood draw to examine levels of selected markers of inflammation, stress, and immune function.

The PRIME-MD will be used as part of our medical screening procedure. It was developed by [name] and colleagues to assist general practitioners in the diagnosis of minor psychiatric disorders. The questionnaire consists of two parts, a self-report patient questionnaire, and a series of interview models for mood disorder, anxiety disorder, psychosomatic disorder, alcohol abuse and eating disorder. It shows good reliability and validity (70,81)

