## ****The Carroll Depression scale is a 21 item scale which asks respondents to endorse multiple facets of depression. We have used this in our previous work and are impressed with its performance. It has good reliability and validity. (14,28).****

The study also includes a 6-month follow-up at which time the treatment group will have received 2-months of bi-weekly treatment and 4 months of weekly treatment. This treatment dose was determined from previous studies and the clinical experience of our team. The wait-list group members will have received 2 months of study attention while they served as the control component of the design. These wait list members then receive 4 months of weekly of courtesy acupuncture. Due to the unbalanced treatment schedule across the wait list and treatment groups they are not directly comparable. Yet preliminary data can be attained from each of the groups using within-groups comparisons, and student’s t-test comparisons of means. For example, changes in the wait-list scores from the main outcome timepoint (2 months) to 6 months can inform future trials considering necessary dose of treatments by highlighting the effects of weekly treatment. In this same way, we may find that while the active treatment group received more frequent sessions during the first 2 months of treatment, the 4 months of weekly treatment carry benefit as well.

19. Data Management:

Methods used for data collection:

To maintain patient confidentiality, study staff will maintain 3 databases. The first will be used for screening and patient communication only and will include necessary patient contact information. The second database will be used to maintain scores on study instruments and will not contain identifying information. A third database will be maintained to track the acupuncture treatments by volunteer identification number and will also contain no identifying information.

Data collection forms are listed in section “B. Surveys, Questionnaires, and Other Data Collection Instruments”. Our main outcome is the physical component of the Sf-36 (53).

Confidentiality:

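### Within-arm change is given an inferential role it cannot carry: unranked beside the between-arm tests for the CDC clusters at 2 months, and read as an effect of weekly treatment at 6 months

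*Protocol*

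**What the plan says.** All of this is in section 18, Data Analysis, of the protocol.

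- **Primary outcome, 2 months.** The test is between arms: "Statistically we will test mean differences between groups following 2 months of treatment using" Student's t-tests at alpha 0.05.
- **Secondary outcomes in general.** "Analyses of secondary outcomes will include a test for mean differences between groups using" Student's t-tests, also at alpha 0.05.
- **CDC clusters.** "Our secondary analyses will include a within-groups comparison within CDC clusters for changes baseline to endpoint (2 months of treatment". Cluster A is measured by the Multidimensional Assessment of Fatigue, cluster B by the Profile of Mood States and cluster C by the McGill Pain Scale.
- **6 months.** The protocol states the limitation itself: "Due to the unbalanced treatment schedule across the wait list and treatment groups they are not directly comparable". It continues: "Yet preliminary data can be attained from each of the groups using within-groups comparisons". It then gives an example: "changes in the wait-list scores from the main outcome timepoint (2 months) to 6 months can inform future trials considering necessary dose of treatments", because the change is taken to highlight the effects of weekly sessions. It adds that the weekly phase may also prove beneficial in the treatment arm.

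Section 15 gives the treatment arm two sessions a week for 2 months and then one a week for 4 months. The wait-list is offered weekly sessions from month 2 to month 6.

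**The concern.** Up to 2 months the trial has a concurrent randomised control. A before-after test inside one arm does not use it. Section 18 names both kinds of analysis for secondary outcomes and singles out the within-arm one for the three symptom domains that define the illness, without ranking them. A report could then claim benefit for fatigue, mood or pain from a within-arm p-value while the between-arm test shows nothing.

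The 6-month text goes further. It attributes a change with no concurrent control to weekly treatment and offers it as information on dose. In the wait-list, that change mixes any effect of weekly sessions with expectation on starting an awaited, open-label treatment and with the passage of time. In the treatment arm, it also mixes in carry-over from the twice-weekly phase.

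The protocol supplies the routes to bias. Section 8 describes an unblinded design with a wait-list. Section 10 requires at least one severe symptom in each cluster, which invites regression to the mean on the domains that the cluster scales measure. The cluster scales are questionnaires answered by volunteers who know their arm.

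**Working it through.** The protocol gives no figure for the within-arm analyses, so there is none to reproduce. The power statement in section 12 concerns the between-arm primary test and is not used here.

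**Inputs**

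- Completers per arm: 60 (section 12). The dropout step reproduces: 60 / 0.90 = 66.7, rounded up to 67 enrolled.
- SD of change: 20 points, stated in section 12 for the SF-36 Physical Component Summary. No SD is given for the three cluster scales, so this is an illustration on a different scale.
- True treatment effect: zero.
- Drift, the mean improvement common to both arms: 3, 5 or 7 points. This is an assumption.
- Alpha 0.05, two-sided. The protocol does not state sidedness.

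**Smallest significant within-arm change**

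SE = 20 / √60 = 2.58. Threshold = t(0.975; 59) × SE = 2.001 × 2.58 = 5.17 points. With all 67 enrolled it is 1.997 × 20 / √67 = 4.88 points.

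**Chance of a positive within-arm test with no treatment effect**

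One-sample t-test, noncentral t, noncentrality = drift / SE:

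| Assumed drift | In SDs of change | Noncentrality, n = 60 | Within-arm positive, n = 60 | Same, n = 67 |
|---|---|---|---|---|
| 3 | 0.15 | 1.16 | 21% | 23% |
| 5 | 0.25 | 1.94 | 48% | 52% |
| 7 | 0.35 | 2.71 | 76% | 81% |

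**Between-arm test under the same drift**

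A common drift cancels in the difference, so the error rate stays at 5%. Simulation with 20,000 runs and 60 per arm gave 4.9% at a drift of 0.20 SD and 5.0% at 0.35 SD.

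**One arm significant, the other not**

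With a 5-point drift in both arms and n = 60, the probability is 2 × 0.478 × 0.522 = 0.50. Half of such trials would show a pattern easily misread as a treatment effect.

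**Is a drift of this size plausible?**

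Equal SDs of 20 for baseline and change imply, if the follow-up SD is also 20, a correlation of 1 − 20² / (2 × 20²) = 0.5. If volunteers enter 0.5 SD worse than their usual level (an assumption), regression to the mean gives a drift of (1 − 0.5) × 0.5 = 0.25 SD, or 5 points, and so the 48% above. With assumed correlations of 0.7 and 0.8 the chance is 31% and 23%. Entering 0.25 SD worse gives 9% to 16%; entering 1 SD worse gives 67% to 97%.

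These regression figures bear on change from baseline to 2 months. For change from 2 to 6 months, much of the regression that follows selection at entry may already have occurred. Expectation, time and carry-over are the main concerns there.

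**The case against.** The strongest reply is that the randomised comparison is already planned. Section 18 provides between-group t-tests for secondary outcomes, and the three cluster scales are among the measures collected at baseline, endpoint and follow-up. The within-group comparison is something the secondary analyses include, not the only one. This stands. A reader might infer that the cluster results rest on within-arm change alone, and the text does not support that. What remains is that the two analyses are not ranked.

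Second, the 6-month text is cautious: it admits non-comparability, calls the data preliminary and points to future trials. This also stands, so these are not planned conclusions. But caution about status does not repair the attribution, since uncontrolled change cannot isolate an effect of weekly sessions even as a preliminary estimate.

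Third, a reader might infer two further faults:

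- **A between-arm t-test at 6 months.** The sentence speaks of data from each of the groups, which points to tests within each arm. No between-arm test at 6 months is clearly stated.
- **A contaminated randomised contrast for biomarkers.** Section 17 plans "ANOVA repeated measures for the overtime changes in immune status" and has a third sample taken after the wait-list has started acupuncture. It states no randomised group-by-time contrast, so there is none to fault. The biomarkers are also laboratory measures, so the self-report argument does not extend to them.

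Fourth, the size rests on assumption. The drifts have no source in the protocol, the SD belongs to the primary outcome, and section 6 describes the illness as stable at 5 and 10 years. That weakens natural course as an explanation, but not expectation or regression to the mean over 2 months. The 28% of wait-list patients with adequate relief at 3 weeks in the team's irritable bowel trial shows that untreated volunteers can report improvement. It is a proportion in another condition and cannot set the drift.

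**Conclusion.** The point holds in limited form. For fatigue, mood and pain at 2 months, the protocol plans both a valid between-arm test and a within-arm comparison and does not say which supports a claim of benefit. At 6 months it reads uncontrolled change as an effect of weekly treatment and as relevant to dose, which the design cannot support.

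Under no treatment effect, the illustration gives a positive within-arm test about 21%, 48% or 76% of the time for drifts of 3, 5 or 7 points, against 5% for the between-arm test. This assumes 60 completers per arm, the SF-36 physical score's SD of change of 20, and the same drift in both arms. It shows that within-arm tests can be significant without an effect, not that they will be, and it is not an estimate for the cluster scales. The primary analysis is between arms and is not touched.

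**What to change.** Three changes of wording, in section 18 or in the statistical analysis plan:

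1. State that the between-arm comparison at 2 months, adjusted for the baseline score already collected, is the inferential analysis for the fatigue, mood and pain scales.
2. Report within-arm changes at 2 and 6 months descriptively, as means with confidence intervals for each arm, and state that significance in one arm and not the other is not evidence of a treatment effect.
3. Remove the sentences that attribute 2-to-6-month change to weekly treatment or use it as evidence on necessary dose.

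The cost is wording only. The visits, instruments, sample size and primary test stay as they are. What is lost is a 6-month dose inference that the design could not have supported.
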